## Abstract

**Background:**

Parkinson’s disease (PD) is the second most common neurodegenerative disorder and, according to the Global Burden of Disease estimates in 2015, was the fastest growing neurological disorder globally with respect to associated prevalence, disability, and deaths. Information regarding the awareness, diagnosis, phenotypic characteristics, epidemiology, prevalence, risk factors, treatment, economic impact and lived experiences of people with PD from the African perspective is relatively sparse in contrast to the developed world, and much remains to be learned from, and about, the continent.

**Methods:**

Transforming Parkinson’s Care in Africa (TraPCAf) is a multi-faceted, mixed-methods, multi-national research grant. The study design includes multiple sub-studies, combining observational (qualitative and quantitative) approaches for the epidemiological, clinical, risk factor and lived experience components, as appropriate, and interventional methods (clinical trial component). The aim of TraPCAf is to describe and gain a better understanding of the current situation of PD in Africa. The countries included in this National Institute for Health and Care Research (NIHR) Global Health Research Group (Egypt, Ethiopia, Ghana, Kenya, Nigeria, South Africa and Tanzania) represent diverse African geographies and genetic profiles, with differing resources, healthcare systems, health and social protection schemes, and policies. The research team is composed of experts in the field with vast experience in PD, jointly led by a UK-based and Africa-based investigator.

**Discussion:**

Despite the increasing prevalence of PD globally, robust data on the disease from Africa are lacking. Existing data point towards the poor awareness of PD and other neurological disorders on the continent and subsequent challenges with stigma, and limited access to affordable services and medication. This multi-site study will be the first of its kind in Africa. The data collected across the proposed sub-studies will provide novel and conclusive insights into the situation of PD. The selected country sites will allow for useful comparisons and make results relevant to other low- and middle-income countries. This grant is timely, as global recognition of PD and the public health challenge it poses builds. The work will contribute to broader initiatives, including the World Health Organization’s Intersectoral global action plan on epilepsy and other neurological disorders.

**Trial registration:**

https://doi.org/10.1186/ISRCTN77014546.

**Supplementary Information:**

The online version contains supplementary material available at 10.1186/s12883-023-03414-0.

## Background

The population of Africa is growing and ageing faster than any other region in the world [1]. The African population aged 65 + is predicted to grow to 570 million by 2100 (for context, the population of all high-income nations of the world is projected to reach 387 million by 2100) [1]. Sub-Saharan African countries will contribute to over half of the global population increase through 2050. This population expansion and demographic shift is inadvertently accompanied by an increase in the burden of non-communicable ageing-related neurological diseases such as Parkinson’s disease (PD) and dementia [2]. Yet ageing, ageing-related issues, and chronic conditions associated with later life, are not adequately prioritised by most African countries. This is despite the abundance of evidence indicating the significant impact (e.g., disability and dependency) attributable to such conditions, including neurodegenerative diseases [2, 3]. PD is the second most common neurodegenerative disorder and, according to the Global Burden of Disease estimates in 2015, was the fastest growing neurological disorder globally with respect to the associated prevalence [4], disability and deaths [5]. The high burden is fuelled by increasing longevity, the effects of industrialisation and environmental factors (for instance, pesticides, air pollution and solvents), and genetic susceptibility [6].

PD demonstrates significant heterogeneity in its causation (e.g., genetic, and environmental risk factors), access to specialised care and treatments and, inadvertently, quality of life and outcomes. Health disparities can affect patient outcomes negatively, and the social impact may vary across cultures [7, 8]. Information regarding the awareness, diagnosis, phenotypic characteristics, epidemiology, prevalence, risk factors, treatment, economic impact and lived experiences of people with PD from the African perspective is relatively sparse in contrast to the developed world, and much remains to be learned from, and about, the continent [7–12].

There have been few PD prevalence studies (most from several decades ago) and no community-based incidence studies in sub-Saharan Africa (SSA) [13–15]. Methodological flaws including the small population sizes surveyed and preponderant reliance on hospital-based data have given the erroneous impression that PD is rare in Africa. The recently published World Health Organization (WHO) technical brief, +‘Parkinson disease: a public health approach’, [16] alludes to the inconsistent data available on PD from low- and middle-income countries (LMICs), and the consequent difficulty of estimating the true burden in Africa or providing convincing data to motivate governmental policy makers and donor agencies to prioritise PD on the continent. Better understanding of the prevalence of PD in communities would justify prioritising PD, inform national policies, improve awareness of the disease, improve diagnostic rates, and access to health services, and drive the focus on providing access to pharmacological and non-pharmacological treatments (e.g., physiotherapy). Until now, there has only been one large scale prevalence study of PD in SSA, based on a house-to-house survey in Hai, Tanzania, in which less than a quarter of people with PD (PwP) had previously been diagnosed [17]. Furthermore, identifying the challenges and needs of PwP and their families in different countries and contexts [7, 8] would drive the narrative for local evidence-based policies [3].

Africa faces a stark gap in the provision of appropriate neurological workforces and trained physicians [18], care, rehabilitation and treatment, making life for PwP very difficult [19]. Awareness about PD is generally very low among the population [8, 20, 21] and healthcare professionals, resulting in under- and delayed diagnosis [10]. Exploring efficient and effective methods for diagnosing PD [22] (including use of telemedicine [23, 24] and/or novel biomarkers) could facilitate diagnosis at the primary care level, while offering opportunities for early management [16]. Sustainable medication is largely inaccessible and unaffordable across the continent [18, 25–28], however, investigations into alternative sources of levodopa (e.g., *Mucuna Pruriens* (MP)) have yielded positive results [29, 30].

Exploring pathophysiological mechanisms and the genetic aetiology of PD has the potential to improve understanding of susceptibility, environmental clustering and response to medication [9]. The developments in genome wide association studies (GWAS) have largely excluded genetically diverse populations [31]. A GWAS of PD among black Africans could provide a valuable source for finding novel genetic determinants that will inform new therapeutics that may eventually benefit patients from all populations [32, 33]. Mutations in genes commonly associated with PD, such as the Leucine Rich Repeat Kinase 2 (*LRRK2*) gene have demonstrated considerable regional variability, and have been virtually absent in black Africans from sub-Saharan Africa in studies reported to date [34–37]. This suggests the strong possibility that other yet undiscovered genetic factors may be at play. For example, the recently identified novel African-ancestry genetic risk factor in *GBA1* [38]. Identifying environmental risks for PD is also crucial [39, 40], and may identify a pathway to implement policy change to reduce exposure. PD is increasingly being referred to as a ‘man-made’ disease [41], with pesticides [42, 43] receiving substantial attention as an environmental risk factor for the development of PD. There is also strong evidence for important metabolic interactions between the gut microbiome, the gut, the immune system, and the brain [44–48].

Considering the evidence presented, this study protocol outlines the United Kingdom (UK) National Institute for Health and Care Research (NIHR) Global Health Research Group (GHRG) on Transforming Parkinson’s Care in Africa (TraPCAf) (Award No. NIHR133391). The NIHR is a major funder of high-quality global health research that addresses the diverse health needs of people in LMICs and supports the objectives of the UK Aid Strategy and the United Nation’s Sustainable Development Goals (SDGs) 2015–2030. The overarching aim of this research grant is to transform the landscape of PD diagnosis, treatment, and care across Africa. The protocol can also be accessed through the ISRCTN registry (https://doi.org/10.1186/ISRCTN77014546), where updates on the progress of the study will be documented.

## Methods

TraPCAf is a multi-faceted, mixed-methods, multi-national research grant. We report the study methods and design using an adaptation of the Standard Protocol Items: Recommendations for Interventional Trials (SPIRIT) guidelines [49, 50]. The study design includes multiple study aspects, combining observational (qualitative and quantitative) approaches for the epidemiological, clinical, risk factor and lived experience components, as appropriate, and interventional methods (clinical trial component). A cross-sectional cohort design is employed for the observational components, while a double-blind randomised controlled trial design is used for the interventional component.

### Aim and research questions

The aim of TraPCAf is to describe and gain a better understanding of the current situation of PD in Africa, addressing the following seven key research questions:What is the prevalence of PD in Africa?Are there unique risk factors (genetic and/or environmental) for PD in Africa and are there lessons about PD in general that we can learn from the African perspective?How can rates of PD diagnosis be improved?Does the clinical phenotype of PD in Africa differ from what has been reported in other populations?How can the quality of PD management in Africa be improved?How can affordable and sustainable treatment for PD be provided in Africa?What is the current lived experience of people with PD, and their families, in Africa?

### Study setting

Seven countries are included in this NIHR GHRG (Egypt, Ethiopia, Ghana, Kenya, Nigeria, South Africa and Tanzania) (Fig. 1) representing diverse African geographies and genetic profiles, with differing resources, healthcare systems, health and social protection schemes, and policies. This multi-country study will be carried out in two research settings, namely within the community and in hospitals (neurology clinics).

**Fig. 1 Fig1:**
[figure not shown]
TraPCAf participating countries and sites marked with red box

All seven countries will be involved in outpatient recruitment (see Table 1 for country sites). These research sites were selected based on the track record of research active clinicians, with an interest in PD, able to identify eligible individuals attending outpatient clinics. All hospitals included in the study are government, university-affiliated, or charitable organisations (not private), capturing data from most of the population.

**Table 1 Tab1:** TraPCAf participating sites and outpatient locations

Country	Location	Outpatient site
Egypt	Cairo	Ain Shams University Hospital
Ethiopia	Addis Ababa	Tikur Anbessa Specialised Hospital
Ghana	Accra	Korle Bu Teaching Hospital
	Kumasi	Komfo Anokye Teaching Hospital
	Sogakope	Richard Novati Catholic Hospital
Kenya	Nairobi	Kenyatta National Hospital
Nigeria	Lagos	College of Medicine, University of Lagos
South Africa	Durban	Inkosi Albert Luthuli Central Hospital
Tanzania	Moshi	Kilimanjaro Christian Medical Centre
	Dar es Salaam	Muhimbili Mloganzila Hospital

The prevalence studies will be conducted in Tanzania, Kenya, Nigeria, and Ghana (as described below), selected based on the lack of epidemiological studies, the availability of infrastructure and delineated populations for a prevalence study (i.e., existence of a demographic surveillance system or a known denominator population in representative rural/urban populations) and the facilities and staff with prior experience to undertake a house-to-house survey.

### Study design

The study involves multiple study aspects (Table 2) that will be implemented across the seven countries (Table 1) in order to address the seven research questions above. In all seven countries, participants will be recruited through neurology outpatient clinics. In 4 countries (Ghana, Kenya, Nigeria, and Tanzania) participants will also be recruited through community-based prevalence studies.

**Table 2 Tab2:** Overview of TraPCAf sub-studies

Research question	Outline of work	Study component	Study details
1. What is the prevalence of PD in Africa?	Community, door-to-door prevalence studies in 4 sites	Door-to-door household survey and clinical exam	Community screening and clinical examination.
2. Are there unique risk factors (genetic and/or environmental) for PD in Africa and are there lessons about PD in general that we can learn from the African perspective?	Exploring the biological mechanisms of PD, conducting genome-wide association and exploring the role of the microbiome and pesticide exposure in PD	a) DNA analysis	Collection and analysis of blood and saliva samples.
		b) Microbiome and metabolite analysis	Collection and analysis of stool and buccal (cheek) samples.
		c) Pesticide, heavy metal and trichloroethylene analysis	Collection and analysis of water, soil, and urine samples.
3. How can rates of PD diagnosis be improved?	Development and assessment of aids to diagnosis, including use of screening tools, technologies for gait assessments, and the role of biological samples as possible diagnostic tools	a) Biological diagnostic tools	Collection and analysis of alpha synuclein in blood plasma, blood serum and saliva samples. Collection and analysis of sebum samples.
		b) Technology diagnostic tools	Collection and analysis of gait assessments. Collection and analysis of neuromotor pen data. Collection and analysis of Optical Computerised Tomography (OCT) data. Collection and analysis of smartphone application data.
4. Does the clinical phenotype of PD in Africa differ from what has been reported in other populations?	Phenotype PD using clinically validated scales and understand progression of PD by following up PwP in outpatient settings	a) Clinical assessment	Clinical examination.
		b) Technology for monitoring progression	Collection and analysis of gait assessments. Collection and analysis of smartphone application data.
5. How can the quality of PD management in Africa be improved?	Understanding current management and improving the management of PD through training	a) Economic evaluation	Economic evaluation of current care and services.
		b) Capacity building	Understanding the role of video examination and telemedicine in PD care. Training of healthcare professionals.
6. How can affordable and sustainable treatment for PD be provided in Africa?	Comparing *Mucuna Pruriens* versus levodopa/carbidopa for the treatment of PD, including an economic evaluation to assess cost-effectiveness	Randomised controlled trial (RCT)	Randomisation to MP or levodopa/carbidopa. Economic evaluation.
7. What is the current lived experience of people with PD in Africa?	Exploring the lived experience of PD through qualitative interviews, the development of information packages and educational campaigns, and the establishment of support groups	a) Qualitative interviews	Analysis of interviews with PwP, family members and stakeholders.
		b) Community education	Development and evaluation of information packages. Development and evaluation of educational campaigns.
		c) Support groups	Development and evaluation of support groups for PD.

#### Processes for recruitment

PwP identified through outpatient clinics, and through prevalence studies, will be invited to participate in TraPCAf, will be provided with information sheets on each of the different aspects of the research (see Table 2), and be able to consent to particular study aspects. The clinical assessment (part of RQ4) is the minimum involvement a participant can have. Consenting participants can, but do not need to, participate in all study aspects. Furthermore, 2 healthy population controls of the same ethnicity, matched for gender and age will be recruited for every 1 PwP, providing the same biological and environmental samples as PwP (RQ2 and RQ3), and undergoing the same clinical assessments (RQ4).

The inclusion criteria for the prevalence studies are:1. Consenting resident in the delineated community for at least 12 months prior to the date of survey.2. Age 18 years or older for Tanzania, Kenya, Ghana (no upper limit) and > 40 for urban Lagos site.

Inclusion criteria for PwP in all studies are:1. Consenting adults aged 18 years or older (no upper limit) diagnosed with PD based on UK Parkinson’s Disease Brain Bank (UKPDBB) clinical diagnostic criteria [51] of any stage.2. For the *Mucuna Pruriens* trial, PwP should be treatment naïve (summary of inclusion criteria detailed in RQ6 section below).

Inclusion criteria for healthy controls are:1. Consenting healthy, neurologically normal (assessed at in-person physical examination) adults aged 18 years or older (no upper limit) who are age, gender and ethnicity matched (per country).

Prospective participants will be excluded if they do not consent or lack capacity to consent (clinical judgment), and/or are physically unable to complete study procedures due to advanced disease and physical disability. Participants will provide details of medical comorbidities, if known, during the clinical examination.

### Group establishment

Group establishment began before the awarding of the grant, during the proposal development phase. This involved bringing together experts from across the seven partner countries to develop the aims, research questions and study methods of the grant. Importantly, this development was guided by our community engagement and involvement (CEI) team.

CEI work ensured the research proposal was designed with, and for, people with PwP and their families. A 2 hour virtual CEI meeting was held with 16 representatives from Nigeria, Kenya, Ghana, and Ethiopia during proposal development to understand their needs, challenges and priorities, their interest and willingness to participate, introduce the proposed research and solicit feedback on the relevance, approach, applicability and objectives. For example, the research team highlighted the challenge of diagnosing people in a prevalence study in contexts where there may not be access to affordable or sustainable drug treatment. However, PwP felt that knowing a diagnosis would give people a better chance to manage the disease, avoiding perceptions associated with witchcraft. Considering this, we are confident that understanding the prevalence of PD across the sites is vital, and knowing a diagnosis may outweigh the challenges of medication accessibility. The CEI team also echoed the need for information about PD burden to push for local policy changes.

Post-award, the group establishment phase has involved ethics application submissions, mapping research priorities, acquiring necessary consumables, a review of existing literature on PD from participating countries, and the planning of CEI activities in-country. The role of CEI in this project is to improve the equality, efficacy and impact of responses and services by ensuring that PwP are active stakeholders in the deliberations, design, decision-making, implementation, and dissemination of the project. This will be monitored using the Community Engagement Process Index. Working with CEI representatives from each country ensures that our engagement is context specific and localised, taking into account national and regional considerations, while recognising similarities and trends across communities and nations.

### Study components

The following sections describe the details of the studies outlined in Table 2*,* addressing research questions 1–7.

All biological samples will be collected by a research nurse at a clinic visit, unless otherwise indicated. All sites have a material transfer agreement with Newcastle University and collected samples will be shipped to Newcastle University for analysis in labs with relevant expertise. Sites have the option to aliquot samples for analysis in situ and for capacity building with expert support and training.

#### RQ1. Prevalence studies in Ghana, Kenya, Nigeria, and Tanzania

To estimate prevalence of PD and/or parkinsonism in Ghana (South Tongu district, Volta region, population 113,114), Kenya (Kilifi, population 300,000), Nigeria (Lagos, subset of population of 1.8 million), and Tanzania (Hai region, population 180,000), door-to-door household screening will be carried out by local, trained health workers in their designated areas/villages. Information recorded will include village name and precise geographical location, head of household, date of visit, name of household member, age, and sex. The head of household will report on behalf of the household (if they are not present, anyone over the age of 18 will be able to respond on the household’s behalf). Data on PD will be collected using an adapted screening tool (from methodology initially described by Dotchin et al. (2008) in Tanzania [17]) as follows:Do you walk more slowly than other people your age?Do your arms or legs shake?Do you shuffle or take short steps when you walk?Do you fall easily?Has anyone told you that you have Parkinson’s disease?

Any positive responders will be reviewed by a study clinician in the community to determine likely diagnosis and advised appropriately. If it is thought they might have PD, they will be invited to an in-person physician assessment and neurology examination to determine diagnosis. Those found not to have PD (or other neurological condition) will be provided with referral advice to an appropriate healthcare facility. Those diagnosed with a neurological condition will be registered at the local clinic for follow-up care. All individuals diagnosed with PD during the prevalence studies will be invited to participate in further study aspects.

The primary outcome measures for the prevalence study will be the number of people with idiopathic PD per 100,000 of the population studied in each country [52], with age standardisation to the WHO population. We will also be reporting on the number of vascular parkinsonism cases per 100,000 population – in view of the high rates of undiagnosed and untreated hypertension in SSA, we expect there may be high rates of vascular parkinsonism. The secondary outcome measure will be sex-specific prevalence of PD in Africa (measured as number of male and female per 100,000 population), again with age-standardisation.

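### The examination that settles the diagnosis is offered only for suspected PD, so the vascular parkinsonism rate per 100,000 may be undercounted or rest partly on unconfirmed diagnoses

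*Protocol article*

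**What the plan says.** Everything decisive is in one section of the protocol article, RQ1 (prevalence studies in Ghana, Kenya, Nigeria and Tanzania).

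- **Aim:** "To estimate prevalence of PD and/or parkinsonism in Ghana" and in the three other countries.
- **Primary outcome:** "The primary outcome measures for the prevalence study will be the number of people with idiopathic PD per 100,000".
- **Further outcome:** "We will also be reporting on the number of vascular parkinsonism cases per 100,000 population". The stated reason is untreated hypertension in the region: "we expect there may be high rates of vascular parkinsonism".
- **Stage 1:** a door-to-door household screen of five questions.
- **Stage 2:** "Any positive responders will be reviewed by a study clinician in the community to determine likely diagnosis and advised appropriately".
- **Stage 3:** "If it is thought they might have PD, they will be invited to an in-person physician assessment and neurology examination to determine diagnosis".
- **What follows:** "Those found not to have PD (or other neurological condition) will be provided with referral advice to an appropriate healthcare facility"; and "Those diagnosed with a neurological condition will be registered at the local clinic for follow-up care".

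The section on data analysis and management adds that prevalence is expressed over the denominator population.

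**The concern.** The article itself separates a likely diagnosis, reached in the community, from a diagnosis determined at the in-person examination. Only suspicion of PD opens the second step. That condition serves the idiopathic PD outcome. It does not serve the vascular outcome, because a vascular case recognised as such in the community does not meet it.

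At stake is the meaning of a rate that the authors expect to be high. Its denominator is the whole surveyed population, while its numerator passes through a filter designed for a different disease. How many vascular cases pass depends on how the local clinician draws the line between the two conditions. The Background says that awareness of PD among healthcare professionals is low, and the Discussion looks forward to comparisons between country sites. A difference in the vascular rate between two countries could then reflect clinician judgement rather than disease frequency.

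**Working it through.** The article gives no figure for this outcome, so there is nothing to reproduce. The check traces one kind of person through the stages and then bounds the effect.

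**Trace.** Take a screen-positive person with vascular parkinsonism.

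1. The community clinician reviews them, as for every positive responder.
2. If the clinician thinks PD is possible, they are invited to the examination and can be diagnosed there as vascular.
3. If the clinician judges them vascular and not PD, no sentence sends them to the examination. They may be among those registered for follow-up with another neurological condition, but the text does not say at which stage that diagnosis is made or whether it makes them a counted case.

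**Inputs (assumed; the article states neither).**

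- g = share of screen-positive vascular cases referred as possible PD, from 0 to 1.
- c = share of the non-referred vascular cases that are still counted from the community review, from 0 to 1.
- The examination is assumed to classify correctly.

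**Formulas.**

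- Counted share = g + (1 − g)c
- Undercount = 1 − counted share = (1 − g)(1 − c)
- Unconfirmed share of the counted cases = (1 − g)c / [g + (1 − g)c]

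| g | c | Counted share | Undercount | Unconfirmed among counted |
|---|---|---|---|---|
| 0.3 | 0 | 0.30 | 70% | 0% |
| 0.5 | 0 | 0.50 | 50% | 0% |
| 0.8 | 0 | 0.80 | 20% | 0% |
| 0.3 | 0.5 | 0.3 + 0.35 = 0.65 | 35% | 0.35/0.65 = 54% |
| 0.5 | 0.5 | 0.5 + 0.25 = 0.75 | 25% | 0.25/0.75 = 33% |
| 0.8 | 0.5 | 0.8 + 0.10 = 0.90 | 10% | 0.10/0.90 = 11% |
| 0.3 | 1 | 1.00 | 0% | 70% |
| 0.5 | 1 | 1.00 | 0% | 50% |
| 0.8 | 1 | 1.00 | 0% | 20% |

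For a given g, the undercount runs from 0 (c = 1) to 1 − g (c = 0). As it shrinks, the unconfirmed part grows. Unless every vascular case is referred (g = 1), at least one of the two problems is present.

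**Between countries.** Suppose two countries have the same true rate, with g = 0.3 in one and 0.8 in the other. With c = 0 the reported rates stand in the ratio 0.30/0.80 = 0.375. With c = 0.5 the ratio is 0.65/0.90 = 0.72. With c = 1 the referral rule creates no difference in the count, but 70% of cases in one country and 20% in the other are unconfirmed.

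The calculation covers screen-positive cases only. It ignores cases that the household screen misses and people wrongly labelled vascular at the community review. The latter would push an unconfirmed count upward.

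**The case against.** The strongest reply has four parts.

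- **Every positive responder is seen.** The community review is not conditional on suspected PD and yields a likely diagnosis. The text also foresees other neurological diagnoses and registers those people. This stands: a reader might infer that no visit measures vascular parkinsonism, and the article does not support that.
- **The threshold is low.** Possible PD is a wide door, and telling vascular from idiopathic disease is a natural task for the examination behind it. This partly stands: vascular cases that resemble PD will get there. But the section distinguishes PD from parkinsonism in its aim and idiopathic PD from vascular parkinsonism in its outcomes, so the condition cannot simply be read as covering parkinsonism of any cause.
- **An undercount is not certain.** A reader might infer that the vascular rate must come out too low, or that a better clinician must produce a lower one. Both follow only if no community-review diagnosis is ever counted (c = 0), which the article does not say. If such diagnoses count, the weakness is unconfirmed classification, whose direction is unknown. This stands.
- **A condensed article leaves case definitions to the full protocol.** That would answer a complaint about missing detail. It does not answer this one, because the referral rule is stated, the outcome is stated a paragraph later, and the rule does not serve the outcome.

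It is also fair to say that parkinsonism of all causes appears only in the aim and is not a named outcome.

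**Conclusion.** The point holds as a mismatch between a stated ascertainment rule and a stated outcome. People judged in the community to have vascular or other non-PD parkinsonism have no stated route to the examination that determines diagnosis. The vascular rate may therefore be undercounted, or may combine confirmed and unconfirmed cases, and it would depend on clinician judgement that can differ between the four countries.

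The size cannot be fixed from the article. It depends on two unstated quantities and on correct classification at the examination; the percentages in the table are illustrations, not estimates. The trigger suits the primary outcome of idiopathic PD, and nothing here counts against that outcome. The issue should be settled before or during fieldwork, because people who were never examined cannot be reliably reclassified at analysis.

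**What to change.** Widen the condition for the study examination from suspected PD to suspected PD or parkinsonism, and record the final category (idiopathic PD, vascular, other) at that examination. This is a change to case ascertainment, not to treatment or care. It alters one phrase in the RQ1 pathway. The cost is somewhat more attendances at a visit that already exists, by people already screen-positive and already reviewed by a clinician.

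If a site cannot do this, it should report vascular parkinsonism only as cases found among people with suspected PD, or show the community-review diagnoses separately and label them unconfirmed. Neither should be presented as a population prevalence per 100,000. This costs no extra visits but gives up a comparable vascular rate for that site.
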